#### Internal pilot outcomes

The progression criteria will be applied to data collected eight months after the first site is opened to determine the feasibility of the RCT continuing. The progression criteria (site set up, participant recruitment, participant allocation per protocol, and follow-up at 6 weeks) will be assessed by the trial steering committee (TSC) at the end of the following month.

Sheffield CTRU will aggregate RCT data to assess the feasibility of the research and intervention protocols based on the feasibility outcomes shown in Table 1.

#### Participant timeline {13}

The participant timeline is shown in Table 2.

**Table 2 Tab2:** Participant timeline

	Baseline (clinic)	6 weeks (clinic)	12 weeks (clinic)	26 weeks (clinic)	52 weeks (remote)
**Baseline and other covariates**					
Pre-screening form/log (before baseline visit)	X	-	-	-	-
Eligibility form	X	-	-	-	-
Surgery details form	X	-	-	-	-
Informed consent form	X	-	-	-	-
Contact details	X	-	-	-	-
Demographics	X	-	-	-	-
Employment (including sick pay provision)	X	X	X	X	X
Vehicle use	X	-	-	-	-
Randomisation (at baseline)	X	-	-	-	-
**Primary outcome**					
Patient-Rated Wrist and Hand Evaluation (PRWHE)	X	X	X	X	X
**Patient-reported measures**					
Patient Evaluation Measure (PEM)	X	X	X	X	X
Work productivity and activity impairment (WPAI)	X	X	X	X	X
EuroQoL EQ-5D-5L	X	X	X	X	X
Litigation/compensation	-	-	-	-	X
Global rating of change (GRoC)	-	X	X	X	X
Preferences for splint attributes	X	X	-	-	-
**Clinical outcomes**					
Range of movement	X	X	X	X	-
Grip strength	-	-	X	X	-
Splint adherence from heat sensor	-	X	-	-	-
Complications and AE/SAEs	X	X	X	X	X

#### Sample size {14}

The sample size was calculated using the methodology and formula for repeated outcome measures [16]. We assumed the following: (i) 90% power; (ii) 1.67% two-sided significance level (to allow for three head-to-head comparisons between the three randomised groups); (iii) 1 baseline and 4 repeated assessments at 6, 12, 26, and 52 weeks post-randomisation; (iv) a target difference of 6 points [17, 18] in the post-randomisation mean PRWHE scores between any two of three groups; (v) a standard deviation of 20 points for the PRWHE outcome at each post-randomisation time point [9, 16–18]; (vi) an exchangeable correlation or compound symmetry of 0.50 between the repeated PRWHE assessments at 6, 12, 26, and 52 weeks post-randomisation [9, 18]; (vii) 20% attrition. With these input parameters, 114 participants per group are required (3 × 114 = 342 in total). After allowing for 20% attrition, we propose to randomise 429 participants in a 1:1:1 ratio (143 long splint: 143 short splint: 143 mini splint).

#### Recruitment {15}

The anticipated recruitment period is 20 months. The estimated overall recruitment rate is 1.2 per month, with site-specific recruitment rates varying from 0.2 to 3.1. Strategies for achieving adequate recruitment will include training staff on the RCT protocol and providing guidance on how to discuss the RCT with potential participants. A screening log will be completed for non-recruited, potentially eligible patients and monitored closely to identify any recurring reasons for non-consent. We will seek advice from our Patient and Public Involvement and Engagement (PPIE) group, and all patient facing materials used during recruitment will be reviewed by our PPIE group.

### Assignment of interventions: allocation

#### Sequence generation {16a}

Once eligibility has been confirmed, consent acquired, and baseline data taken, the participant will be randomly allocated to either the long splint arm, the short splint arm, or the mini splint arm on a 1:1:1 basis, using a web-based randomisation system provided by Sheffield CTRU. Randomisation allocations will be based on computer-generated pseudo-random lists, stratified by site, with random permuted block sizes.

#### Concealment mechanism {16b}

Randomisation will be completed using a secure, central online randomisation service hosted by the University of Sheffield. Participant ID, site, and confirmation of eligibility and consent will be entered into the randomisation system and the treatment allocation will be confirmed. Allocation concealment will be ensured as the central online randomisation service will not release the randomisation code until the patient has been recruited into the trial.

#### Implementation {16c}

The allocation sequence will be generated by the RCT statistician, who is independent of the participating NHS Trust sites. Randomisation will be done by delegated site staff during the clinic visit and participants will be informed of the outcome verbally. Participants’ GPs will also be informed of their participation in the RCT and their treatment allocation.

## Assignment of interventions: blinding

### Who will be blinded {17a}

In view of the nature of the intervention, patients and their treating clinicians cannot be blinded to treatment allocation. However, to avoid the risk of bias, clinical assessors at sites measuring AROM and grip strength will be blinded to allocation of the participant. The RCT statistician responsible for data analysis will remain blind until the completion of data cleaning. The quality control will be undertaken by an unblinded statistician, who will also attend DMECs, TSCs, and TMGs during the RCT conduct.

### Procedure for unblinding if needed {17b}

Where clinical assessors are inadvertently unblinded, sites will complete an unblinding form and report the unblinding incident to the CTRU RCT manager who will maintain a log of unblinding instances. Site staff will be prompted to record and report any unblinding incidents on the clinical assessment CRFs for each visit.

## Data collection and management

### Plans for assessment and collection of outcomes {18a}

All clinical data will be entered by research site staff onto the CTRU’s in-house data management system (Prospect). Patient-reported outcome measures (PROMs) data (to include the primary outcome assessment) will be completed online by the patient using a tablet in clinic at baseline, 6, 12, and 26 weeks, with paper copies available if this is not possible. PROMs may also be completed remotely via email, post or over the phone where required, if a participant is unable to attend an in person visit. At 52 weeks, all questionnaires will be completed remotely (via email/post or over the phone). 

Complications and adverse events (AEs)/serious adverse events (SAEs) will be assessed at each clinic visit and via phone call at 52 weeks by a delegated member of the research team at each site specific to the participant.

### Plans to promote participant retention and complete follow-up {18b}

Participants who withdraw from RCT treatment will be encouraged to continue as participants in the RCT follow-up. Participants may withdraw their consent to continue with follow-up for the RCT at any time, without providing a reason for this. Any data collected up to the point of the participant’s withdrawal will be retained, and used in the final analysis, and this will be made clear to the patient at the time of consent.

Participants who wish to withdraw from follow-up will be given the option to withdraw only from RCT visits and continue to complete follow-up remotely, where possible. Similarly, participants who do not attend a research follow-up visit(s) may be given the option to complete this follow-up visit remotely. This will ensure lost data is minimised and that the primary outcome is collected in a timely manner. Non-responders to email/postal questionnaires at all time points may be followed up by the CTRU research team using contact details provided by the participant.

The primary outcome is currently collected routinely at some sites, but not at all. Where applicable, if a patient chooses to withdraw from the entire RCT, they will be asked if they are happy for the RCT team to use their routinely collected data in order to inform the primary outcome. This will be optional, but if the patient agrees, it will help to maintain the statistical power and reduce the potential of bias introduced due to missing data when assessing RCT outcomes. Participants with ongoing adverse events at the point of withdrawal will also be asked if they are agreeable for routinely collected data to be used to inform safety outcomes. The RCT team will document this discussion on a RCT specific form and provide the participant with a copy for their records.

Efforts will be made to keep participants engaged in RCT follow-up. Regular updates will be posted on the RCT website and/or communicated via email or newsletter. Vouchers will be provided, and prize draws may take place, for participants who complete follow-up questionnaires. Follow-up visits have been aligned with routine clinic visits where possible, and routine outcome data will be used wherever possible, to minimise the additional burden on participants. Participants will only be considered lost to follow-up if they have not returned the week 52 questionnaires at the point of RCT closure. Where participants do not attend a scheduled appointment, or cannot be contacted to schedule an appointment, questionnaires will be sent via email and contact will be attempted again at each subsequent time point, unless the participant withdraws from the RCT.

### Data management {19} and confidentiality {27}

Participant confidentiality will be respected at all times and the principles of General Data Protection Regulation (GDPR) will be followed. The investigator will ensure that identifiable data is kept securely and protected from unauthorised parties. All patients will be given a unique RCT identifier (participant ID) on entry into the RCT, and this will be used in all future RCT correspondence outside of the direct care team and on data collection forms. Names, email addresses, phone numbers, and addresses where required (if participants prefer to receive paper questionnaires via post) will be collected on the RCT database, to facilitate sending and follow-up questionnaires at the week 52 remote visit, and contacting participants about the qualitative interviews, where consent to do so has been obtained. Access to personal data will be available only to those who need it.

All aspects of data management, including data protection and archiving, will be provided by the University of Sheffield CTRU in accordance with their own standard operating procedures (SOPs). The RCT will use the CTRU’s in-house data management system (Prospect) for the capture and storage of participant data. Project-specific procedures for data management will be detailed in a separate data management plan.

The investigator or delegate at each site will maintain comprehensive and accurate source documents to record all relevant RCT information regarding each participant, in all instances where the database does not form the source data.

### Plans for collection, laboratory evaluation, and storage of biological specimens for genetic or molecular analysis in this trial/future use {33}

Not applicable.

## Statistical methods

### Statistical methods for primary and secondary outcomes {20a} and additional analyses {20b}

Data will be reported and presented according to the CONSORT [19]. All analyses described below will be on the as-randomised (intention to treat) basis, unless specified otherwise. Full details of the statistical analysis will be provided in a separate statistical analysis plan (SAP) which will be finalised prior to the end of follow-up. The SAP will be made available on the trial ISRCTN site. The analysis will be conducted in accordance with CTRU SOPs.

The final analysis will take place after all follow-up has been completed.

Baseline demographic, physical and clinical characteristics, and health-related quality of life data will be described and summarised overall and for the three randomised groups.

### Primary outcome

The primary outcome will be the mean post-randomisation total score on the PRWHE measured at 6, 12, 26, and 52 weeks post-randomisation. The primary effectiveness analysis will compare the post-randomisation PRWHE scores, between the three randomised groups, using a linear mixed model incorporating all post randomisation PRWHE scores (at 6, 12, 26, and 52 weeks) as outcomes, with random effects for centre and subject (to account for the repeated observations per patient), and fixed effects for randomised group, time post-randomisation, and baseline score [20]. We shall assume an exchangeable correlation between the repeated measurements.

Three treatment effect contrasts will be estimated and reported from the linear mixed model: (1) long vs short splint (2); long vs mini splint (3); mini vs short splint. We will estimate 98.3% confidence intervals for the three treatment effects for simultaneous inference and to ensure that all parameters are covered with 95% confidence. This model will include all patients who provide valid PRWHE data for at least one post-randomisation follow-up time point.

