### Methods for additional analyses (e.g. subgroup analyses) {20b}

Subgroup analyses will be performed to explore whether there is heterogeneity in treatment effect for the primary endpoint across the following pre-specified subgroups: sex, employment type, eligibility for occupational sick pay, age category, zone of injury, and tendons repaired.

The subgroup analyses will be performed on the ITT population only. The analysis will be based on the primary analysis model with the addition of an interaction term between the treatment and subgroup to assess the stability of the result in different populations. For simplicity, the interaction between treatment and time will be excluded from this model. Treatment effect estimates for the mean PRWHE post-randomisation scores with 98.3% confidence intervals will be calculated for each sub-group. The results will be displayed graphically using forest plots. No *p*-values will be presented, as it is acknowledged that the trial is not powered for these subgroup analyses, and they are considered exploratory.

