### Methods in analysis to handle protocol non-adherence and any statistical methods to handle missing data {20c}

The impact of missing PRWHE outcome data will be minimised to some extent by using the linear mixed model, which allows the inclusion of intermittent responders in the primary analysis. PRWHE scores for complete and intermittent responders will be compared descriptively. The impact of missing data will additionally be assessed using multiple imputation by chained equations (MICE). Missing outcome and covariate data will be predicted by age, rupture rate, hand dominance, available PRWHE data at other follow-up time points, and any baseline covariates found to be predictive of the outcome data. The estimates of the treatment effects and their associated confidence interval from the imputation model will be graphically displayed alongside the results for the observed data. Additional sensitivity analysis will consider scenarios whereby participants with missing data have outcomes worse than those with available data (missing not at random scenarios). The primary analysis approach will be based on the as-randomised population, analysing participants in their randomised groups regardless of adherence to their randomised intervention.

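### The primary model is valid, but baseline PRWHE is its only patient-level prognostic covariate; adding pre-randomisation age, sex, zone of injury and tendons repaired may gain precision at almost no cost

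*Protocol article*

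**What the plan says.** In the protocol article, the Primary outcome section under Statistical methods specifies a linear mixed model for the 6-, 12-, 26- and 52-week PRWHE scores. It has random effects for centre and subject and "fixed effects for randomised group, time post-randomisation, and baseline score". Centre is there for good reason: site is the only stratification factor (Sequence generation {16a}).

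Three other places bear on the choice of covariates.

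- The participant timeline (Table 2) lists demographics and a "Surgery details form" at baseline. Sequence generation {16a} has allocation follow baseline data collection.
- The subgroup section {20b} names "sex, employment type, eligibility for occupational sick pay, age category, zone of injury, and tendons repaired" as factors for exploring heterogeneity of the treatment effect.
- The missing-data section {20c} says of the multiple imputation: "Missing outcome and covariate data will be predicted by age, rupture rate, hand dominance". It adds PRWHE at other time points and any baseline covariates found to be predictive.

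The sample size section {14} takes a "1.67% two-sided significance level (to allow for three head-to-head comparisons between the three randomised groups"), "a target difference of 6 points" and "a standard deviation of 20 points for the PRWHE outcome at each post-randomisation time point".

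**The concern.** In a linear model, adjusting for pre-specified baseline variables that predict the outcome reduces the residual variance and leaves the target of estimation unchanged. Here the plan conditions on one such patient-level variable. Others will be in the database before allocation, and four of them (age, sex, zone, tendons repaired) must be coded in some form for the subgroup analyses anyway. Because the error rate is split over three contrasts, each tested at 1.67%, extra precision that needs no extra patients is worth having.

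The second strand is missing data, with 20% attrition planned for. The mixed model's missing-at-random condition is given group, time, centre, baseline PRWHE and the observed follow-up scores. The imputation analysis conditions on more, including age. If age is related to both dropout and PRWHE, the primary analysis omits a variable that the plan itself regards as useful for predicting missing scores.

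**Working it through.** **Inputs.** From Sample size {14}: two-sided alpha 0.0167 (0.05/3, z = 2.394), power 90% (z = 1.282), difference δ = 6, SD σ = 20, correlation ρ = 0.50, and "1 baseline and 4 repeated assessments at 6, 12, 26, and 52 weeks post-randomisation". The correlation is stated for the post-randomisation scores. Reproducing the stated n requires the same value between baseline and follow-up, so that is an implicit assumption.

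**Step 1: reproduce the plan's figure.** With four follow-up scores and one baseline score, the variance factor for the baseline-adjusted mean is

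R = [1 + 3(0.5)]/4 − 0.5² = 0.625 − 0.25 = 0.375, so σ²R = 400 × 0.375 = 150.

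n = 2(2.394 + 1.282)² × 150/36 = 112.6 per group.

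Adding the small-sample term z²/4 = 2.394²/4 = 1.43 gives 114.0, the stated 114. Attrition: 114/0.8 = 142.5, rounded up to 143; 3 × 143 = 429, as stated. Without baseline adjustment (R = 0.625), n would be 188 per group, so the calculation already relies on the model's one prognostic covariate and on no other.

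**Step 2: add covariates.** Let q be the share of the remaining variance of the mean follow-up score that the added covariates explain. The document gives no value for q, so the figures below are an assumed range.

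SE = √[2 × 150 × (1 − q)/114]; half-width = 2.394 × SE; power = Φ(6/SE − 2.394); equivalent extra analysed participants = 342/(1 − q) − 342.

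| q (assumed) | SE | 98.3% half-width | Power | Equivalent extra participants |
|---|---|---|---|---|
| 0% | 1.62 | 3.88 | 90.4% | 0 |
| 5% | 1.58 | 3.79 | 91.9% | 18 |
| 10% | 1.54 | 3.68 | 93.4% | 38 |
| 15% | 1.50 | 3.58 | 94.7% | 60 |

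These powers use the normal approximation; with the noncentral t distribution, the q = 0% entry is 90.0%.

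**Step 3: the cost if they explain nothing.** Take about 337 residual degrees of freedom at participant level (342 − 5) and 4 to 6 added parameters. The SE is then multiplied by √(337/333) = 1.006 to √(337/331) = 1.009, a loss of 0.6% to 0.9%. Break-even is at about q = 4/337 = 1.2% to 6/337 = 1.8%.

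**Step 4: compare the conditioning sets.** The primary model has group, time, centre, baseline PRWHE and observed PRWHE. The imputation names age, rupture, hand dominance, PRWHE at other times and any predictive baseline covariates. Of the four proposed covariates, only age is named there. Rupture is recorded as a serious adverse event during follow-up (Adverse event reporting and harms {22}), so it cannot be a baseline covariate in the primary model. Adding age therefore narrows the gap but does not close it.

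**The case against.** The strongest reply is that nothing is broken. The model adjusts for the baseline value of the outcome and includes the only stratification factor. It agrees with the sample size calculation and delivers the planned 90% power on the stated assumptions. Bias and loss of error control are not at issue. All of this stands.

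It is also fair that the gain is modest. At the assumed 5% to 15%, the half-width shrinks by about 0.1 to 0.3 points on a 0 to 100 scale, against a 6-point target. Which covariates to add is partly a matter of judgement.

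A reader might infer from the subgroup section that the protocol already regards these variables as prognostic. It does not: it lists candidate effect modifiers and calls those analyses exploratory, and an effect modifier need not predict outcome. A reader might also take the coding as settled. It is not: the subgroup section uses age in categories and gives no levels for any factor. The exclusion criteria rule out only lacerations of three or more fingers, so a participant with two injured fingers may have a different zone or tendon repaired in each. Finally, an imputation analysis that conditions on more than the primary model is not a defect in itself, and section {20c} also plans missing-not-at-random scenarios.

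What survives is narrower: the fixed effects are stated in the article, the extra variables cost nothing to obtain, and the downside is small and bounded.

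**Conclusion.** The point holds as an efficiency and robustness improvement. The contrasts may be less precise than the baseline data allow. It would be too strong to say that they are, because that depends on prognostic strength beyond baseline PRWHE, which the document does not give. Over the assumed 0% to 15% range, power runs from 90.4% to 94.7% and the half-width from 3.88 to 3.58 points, against a cost of under about 1% of the SE if the covariates are useless. These figures rest on SD 20, correlation 0.50 (including between baseline and follow-up) and 114 analysed per group.

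Two stronger readings are not supported. One is that the primary analysis is invalid or underpowered: it is neither on the protocol's own inputs. The other is that the added covariates would put the primary and imputation analyses on the same missing-at-random footing: hand dominance, rupture and data-selected covariates would still separate them.

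**What to change.** In the primary model, add as fixed effects the pre-randomisation values of age (continuous), sex, zone of injury and tendons repaired. State the levels of zone and tendons repaired, and give one participant-level rule for those with two injured fingers. State how a missing baseline covariate is handled, so that nobody drops out of the primary analysis because of it. Keep the model as now written as a sensitivity analysis.

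The cost is a sentence or two in the protocol or SAP, 4 to 6 degrees of freedom, and the work of fixing the coding. No new data, visits or patients are needed. The change must be made before unblinding. The article leaves room for this: the SAP is to be finalised before follow-up ends (Statistical methods {20a}), and the analysing statistician stays blind until data cleaning is complete (Who will be blinded {17a}).

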### Complications, safety outcomes, and adverse events

The following summaries will be presented: the number and percentages of patients reported as having SAEs in each treatment arm; the number and percentages recorded as having all forms of AEs in each arm; this will be presented as overall and stratified by AE classification. Other complications (e.g. damage to splint, splint modifications) will be presented and reported in a similar way to SAEs.

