## Abstract

**Background:**

Without surgical repair, flexor tendon injuries do not heal and patients’ ability to bend fingers and grip objects is impaired. However, flexor tendon repair surgery also requires optimal rehabilitation. There are currently three custom-made splints used in the rehabilitation of zone I/II flexor tendon repairs, each with different assumed harm/benefit profiles: the dorsal forearm and hand-based splint (long), the Manchester short splint (short), and the relative motion flexion splint (mini). There is, however, no robust evidence as to which splint, if any, is most clinical or cost effective. The Flexor Injury Rehabilitation Splint Trial (FIRST) was designed to address this evidence gap.

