**Discussion:**

FIRST will compare the three splints with respect to clinical efficacy, complications, quality of life and cost-effectiveness. FIRST is a pragmatic trial which will recruit from 26 NHS sites to allow findings to be generalisable to current clinical practice in the UK. It will also provide significant insights into patient experiences of splint wear and how adherence to splinting may impact outcomes.

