### Relative motion flexion splint (Mini)—finger-based splint

Over the last 5 years, there has been a worldwide shift in the management of extensor tendon repairs moving from using a long splint to the relative motion extension splint (RMES) [8]. More recently, the concept of relative motion splinting has also been introduced into clinical practice for flexor tendon repairs. The relative motion flexion (RMFS (mini)) splint positions the affected digit into relative flexion and therefore utilises the quadriga effect to reduce the biomechanical pull on the repaired tendon. It is also worn in combination with a wrist splint for the first 3 weeks in order to limit full extension of the wrist. The mini splint is thought to provide less protection than the long and short splints described above, but the patients’ function may be improved whilst wearing the splint. This may lead to reduced joint stiffness.

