### Secondary outcomes

The scores on the repeated continuous secondary outcomes (e.g. PEM, EQ-5D-5L, AROM, Grip strength, Splint adherence) will be compared between the randomised groups using a similar longitudinal mixed effects linear regression model as described for the analysis of the primary outcome. Treatment effects for each protocol stipulated follow-up points will also be presented.

Adherence to the randomised splint treatment during the first 6 weeks post-randomisation will be estimated from the heat sensor in the splint. Adherence will be summarised for each randomised group using a variety of summary measures (e.g. mean number of hours per day wearing the splint) and mean adherence compared between the group using a linear regression model. As with the primary outcome, three treatment effect contrasts and their associated confidence intervals will be estimated and reported from the model: (1) long vs short splint, (2) long vs mini splint, (3) mini vs short splint.

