^***^Other important medical events that may not result in death, be life-threatening, or require hospitalisation may be considered a serious adverse event/experience when, based upon appropriate medical judgement, they may jeopardise the patient and may require medical or surgical intervention to prevent one of the outcomes listed in this definition

SAEs will require more detailed information to be recorded. For the purposes of this RCT, flexor tendon rupture is considered a medically significant event, and any incidents will be recorded as SAEs.

SAEs must also be reported to the Sheffield CTRU immediately but within a maximum of 24 h of the site becoming aware of the event, unless exempt. The CTRU will coordinate ongoing monthly reporting to the sponsor or as soon as possible if unexpected SAE. The DMEC and TSC will also receive information on all AEs and SAEs, at a frequency agreed with each committee and documented in the appropriate charter/terms of reference.

The following events are expected and, should they meet the criteria for seriousness, do not require reporting to CTRU within 24 h, but should be reported within the time frames specified below:

Within 72 h, for ongoing safety monitoring purposes:Flexor tendon rupture

Before the participants next scheduled follow-up visit:
2.Local pressure areas because of the splint, plaster of paris, or dressings3.Infection leading to:Treatment with oral antibioticsTreatment with intravenous antibiotics either as an inpatient or outpatientRequiring surgical washout4.Stiffness of the affected hand requiring surgery, e.g. tenolysis/arthrolysis5.Scar issues, e.g. hypersensitivity/hypertrophic scars6.Delayed wound healing requiring an extended period of dressing7.Complex regional pain syndrome8.Fixed flexion deformity of the proximal interphalangeal joint (PIPj) or distal interphalangeal joint (DIPj) requiring additional splintage

SAEs which are deemed related to the research and are not expected will be reported to the research ethics committee (REC) who approved the RCT.

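### Complications are to be compared between splints, but the safety section plans only per-arm counts, with no between-arm estimate or interval and no separate line for tendon rupture

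*Protocol article*

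**What the plan says.** The abstract's discussion states that "FIRST will compare the three splints with respect to clinical efficacy, complications, quality of life and cost-effectiveness". Complications and adverse events also appear in the list under Clinical secondary outcome.

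The section on complications, safety outcomes and adverse events sets out the analysis: "the number and percentages of patients reported as having SAEs in each treatment arm", then the same for all AEs, where "this will be presented as overall and stratified by AE classification". Other complications, such as splint damage, are to be reported in a similar way. No contrast, interval or model is given, and rupture is not mentioned.

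Elsewhere the protocol singles rupture out. Under Adverse event reporting and harms, "flexor tendon rupture is considered a medically significant event, and any incidents will be recorded as SAEs", with a 72-hour reporting limit of its own. On the splints, the abstract's background describes them as "each with different assumed harm/benefit profiles", and the section on the relative motion flexion splint says "The mini splint is thought to provide less protection than the long and short splints described above", while function during wear may be better.

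Other outcomes are treated differently. The primary outcome gets three pairwise contrasts with 98.3% intervals. "The scores on the repeated continuous secondary outcomes" are compared using a similar mixed model, and adherence gets three contrasts with intervals. The subgroup analyses get 98.3% intervals although the protocol accepts that the trial is not powered for them. No between-arm analysis is specified for a binary outcome.

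**The concern.** The case for the trial rests partly on a balance between function and protection of the repair. The function side will be reported as three differences with simultaneous intervals. The protection side, as the safety section stands, will be reported as percentages side by side. Whether rupture gets its own row depends on an AE classification that the article does not define.

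Similar percentages in three arms can be taken as evidence of similar safety. At this sample size they could be compatible with a material difference, and no planned interval would show it. The protocol expects its results to inform national hand therapy and hand surgery guidelines, so the precision of the rupture comparison should be visible beside the PRWHE result.

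**Working it through.** **The plan's own figure.** The only sample size calculation is for PRWHE. Inputs from the Sample size section: difference 6, SD 20, four post-randomisation assessments, correlation 0.50, baseline adjustment, 1.67% two-sided, 90% power.

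- Variance of the baseline-adjusted mean: 20² × [(1 + 3 × 0.5)/4 − 0.5²] = 400 × 0.375 = 150 (SD 12.25).
- n per group = 2 × 150 × (2.393 + 1.282)² / 6² ≈ 112.5, so 113 against 114 stated. Power at 114 is 0.904.
- Attrition: 114 / 0.80 = 142.5, so 143 per group and 3 × 143 = 429.

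The figure reproduces to within one participant. It concerns PRWHE only; nothing is stated for rupture.

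**Precision for rupture.** The documents give no rupture rate, so 3%, 5% and 10% are assumptions. With n = 143 per arm and z = 2.393 (the trial's 98.3% level), the half-width for a pairwise risk difference with equal rates is 2.393 × √[2p(1 − p)/143].

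- p = 3%: 2.393 × √(0.0582/143) = 4.8 points
- p = 5%: 2.393 × √(0.0950/143) = 6.2 points
- p = 10%: 2.393 × √(0.1800/143) = 8.5 points

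If only 114 per arm contributed, the half-widths would be 5.4, 6.9 and 9.5 points.

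Equal observed rates of 3% or 5% would therefore leave a doubling inside the interval (4.8 > 3; 6.2 > 5). At 10% the limit falls short of a doubling (8.5 < 10).

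**Power, to show why this should be estimation.** For p against 2p at 1.67% two-sided, power = Φ{p / √[(p(1 − p) + 2p(1 − 2p))/143] − 2.393}.

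- 3% v 6%: Φ(0.0300/0.0245 − 2.393) ≈ 12%
- 5% v 10%: Φ(0.0500/0.0310 − 2.393) ≈ 22%
- 10% v 20%: Φ(0.1000/0.0418 − 2.393) ≈ 50%

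A separate calculation for 5% v 10% gives 21%, and about 748 per arm would be needed for 90% power. A rupture comparison in this trial can be an informative estimate but not a powered test.

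**The case against.** The strongest objection is that the article leaves full statistical detail to a separate SAP. The safety section says which summaries will be presented; it does not say that nothing else will be. The SAP may already contain the contrast. That stands as a limit on the conclusion. It does not remove the point, because the section states a method for a listed secondary outcome, and that method is descriptive while neighbouring sections name contrasts and intervals.

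A reader might infer that the promised comparison of complications cannot be delivered, or that no reported number could reveal a difference. The documents do not support this. Counts by randomised arm are themselves a descriptive comparison, and with the denominators they yield a risk difference and interval by arithmetic. What is missing is prespecification.

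A reader might also infer that the protocol names rupture as the harm expected to separate the splints. It does not. It speaks of differing harm and benefit profiles and of less protection from the mini splint. The complications it ties to particular splints are stiffness, fixed flexion deformity and adhesions for the short splint, and joint stiffness for the mini. Some of these bear on range of movement, which does get a between-group model.

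Nor is rupture ignored. The Discussion says oversight committees saw per-group data including rupture rates, the DMEC can request unblinded data and recommend stopping on safety grounds, and complication proportions enter the long-term economic model, which has a probabilistic sensitivity analysis. None of these is a between-arm rupture estimate in the clinical report.

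Finally, low power for rupture follows from the sample size, and the protocol claims neither power nor equivalent safety for it. That is correct, and it is why the remedy is an interval and not a test.

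**Conclusion.** The point holds as a cheap improvement. Complications are a listed secondary outcome on which a comparison is announced, but the stated analysis stops at per-arm counts and percentages and does not name rupture, an event the protocol always treats as serious and reports on its own timetable. Intervals are already planned for subgroups without power, so lack of power is no reason to omit them here.

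The size depends on assumed rupture rates and 143 analysed per arm: 98.3% half-widths of about 4.8, 6.2 or 8.5 points at 3%, 5% or 10%. At the two lower rates, identical observed percentages would not exclude a doubling. The sample size and primary analysis are unaffected. If the SAP already specifies these contrasts, only the article's wording needs to be aligned.

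**What to change.** In the section on complications, safety outcomes and adverse events, and in the SAP:

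- list rupture of the repaired tendon by 52 weeks as its own line, by randomised arm;
- prespecify the three pairwise risk differences (long v short, long v mini, mini v short) with 98.3% confidence intervals;
- state that these are estimates and not powered tests, so that lack of a clear difference is not read as equal safety.

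Per-arm counts can remain for other adverse events. The interval method can be settled in the SAP; at 3% only about four events per arm are expected (143 × 0.03 = 4.3), so the simple normal formula used above is approximate.

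No new data are needed: "Complications and adverse events" are already assessed at each clinic visit and by phone at 52 weeks. The article says the SAP will be finalised before follow-up ends, so the change is a few lines of text and three intervals. The downside is that the intervals will be visibly wide.
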